The overall aim of the clinical trials (F_clin_, W_clin_) is to investigate short-, medium-, and long-term health effects of a 12-week interactive web-based health program (TK-HC) compared to a 12-week non-interactive web-based health program in physically inactive (F_clin_) and overweight or obese adults (W_clin_). For this purpose, the effects of each web-based health program on primary and secondary outcomes will first be examined. The hypothesis that participation in each health program is associated with improvements will be tested. Second, the difference between the interactive and non-interactive health program will be examined in terms of their effects on primary and secondary outcomes. The hypothesis will be tested that participation in the interactive health program achieves more significant improvements than participation in the non-interactive one. Finally, the impact of program use on program effectiveness will be examined. The hypothesis that higher frequency and intensity of program use leads to better primary and secondary outcomes in comparison to program use of lower frequency and intensity will be tested.

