### 2.3. Interventions

#### 2.3.1. Interactive Web-Based Health Program

The intervention group for both clinical trials (F_clin_, W_clin_) will receive the TK-HC. This multimodal health program comprises different coaching modules to enable personalized health coaching according to the chosen health goal and personal health profile. With an evidence-based foundation, it attempts to meet the requirements of quality-assured prevention programs while providing a high degree of usability through interactive, self-directed, and flexible handling [70]. For the present evaluation of the TK-HC, however, the focus will be on individual coaching modules so that the intervention group of the fitness trial (F_clin_) will receive the “TK-FitnessCoaching” (TK-FC) and the intervention group of the weight loss trial (W_clin_) will get the “TK-WeightLossCoaching” (TK-WC). Both coaching modules are intended to achieve sustainable health effects within a 12-week intervention phase to prevent NCDs in the long term. The TK-FC is specialized in promoting physical activity and physical fitness based on endurance, strength, flexibility, and coordination training. The focus of the TK-WC is to assist users in losing and maintaining weight by following the energy density concept and a balanced, healthy diet.

The TK-HC is structured in the same way for both modules. Before starting the program, the user is guided through a multistep anamnesis to check suitability for the chosen health goal and set up an individually tailored program according to the personal health profile. The TK-WC user selects the preferred weight loss goal (3 or 5 kg). After completing the anamnesis, the user is directed to the program platform, consisting of three main areas. The first area (“My health program”) presents a personal dashboard that forms the central part of the program and accompanies the user in everyday life (Figure 1a,b). Here, the user can view an individual weekly plan of daily activities and an overall 12-week coaching plan based on three phases (phase 1: getting to know and trying out (week 1–3), phase 2: consolidating new behaviors (week 4–6), phase 3: anchoring habits (week 7–12)). The user can flexibly adapt these plans to individual needs by selecting activities from 13 fitness (TK-FC) (Figure 2a) and 12 weight loss (TK-WC) (Figure 2b) activities.

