The fitness activities focus strongly on endurance training (e.g., “I improve my endurance by running”) and strength training (e.g., “I strengthen my muscles according to a recommended training plan”) as well as on flexibility and coordination training (e.g., “I train my flexibility”) and other health-related fitness courses (e.g., “I train yoga according to instructions”, “I train my back”). All training sessions follow the principle “train—log—analyze” and include detailed training introductions and instructions. Depending on the activity, the sessions can be done at home, in the gym, or outdoors. For endurance and strength activities, a standardized fitness test must be completed to classify the training level and thus select an adequate training plan. After six and eleven weeks, it is recommended to repeat this fitness test to measure the training success objectively. Besides all these activities, additional sports activities can be logged.

The weight loss activities concentrate on tasks that support the user in implementing the energy density concept (e.g., “I achieve a green energy density”) and the principles of a balanced, healthy diet (e.g., “I eat fruit two times and vegetables three times a day”). The key activity of the weight loss program is the nutritional protocol, which is automatically scheduled daily into the coaching plan. This tool supports adherence to the energy density concept and orientation on energy balance by displaying energy density, calorie intake, calorie consumption by physical activity, and fluid intake. In addition, this activity includes a daily macronutrient analysis and a cookbook with many healthy recipes. Another pre-planned activity is to log body weight and waist circumference every week.

All fitness and weight loss activities must be logged daily or weekly and can be modified at any time. The TK-FC user can also select weight loss activities, and the TK-WC user can also choose fitness activities. Both users can further link an activity tracker to the program by transferring the daily step count. Overall, the dashboard visualizes daily planned and logged activities, total activities completed per week, current health goal achievement via widgets, notifications to communicate with the user, personalized daily tips, and a support option. The TK-FC also includes a weekly barrier management tool.

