In the second area of the program (“Knowledge”), the user receives evidence-based background information on the respective health goal through a coaching-accompanying knowledge course (“Optimal training” (TK-FC), “Weight loss with energy density concept” (TK-WC)), which is pre-set as a weekly activity in the coaching plan. Moreover, the user can pass other health-related knowledge courses. All courses are split into small articles and are structured interactively using texts, videos, tools, and tests.

Finally, the third area (“My data”) provides an individual analysis profile with visualized data from logged activities as well as the personal health profile and personal data. Furthermore, the user can download the study information and consent form for both the online and the clinical trial and has the option to withdraw participation from the trials and the health program. After program completion, the user gets a coaching summary, and the user can repeat the coaching as often as desired until the end of the study period.

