#### 2.4.3. Other Outcomes

To examine the effects of usage behavior on primary and secondary outcomes, system usage data regarding the participation in the health programs during the intervention phase (frequency (days with logins/week) and duration of program logins (average minutes/login), logged activities (activities/week) (intervention group)) and the follow-up phase (frequency of program logins (days with logins/week)) will be collected and stored by VHG. A secure cloud system will be used to transfer these data to the DoSS [71].

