According to the intention-to-treat (ITT) principle, all randomized cases will be included. In addition, only cases that have followed the per-protocol (PP) principle will be analyzed. While for ITT analysis, missing values will be imputed, in PP (complete case) analysis, only study participants with no missing values for the corresponding outcome will be analyzed. The ITT and PP analysis will be compared. An assessment of completed measurement time points will be used to test whether study participants who have completed all medical examinations differ in the corresponding outcome. Multiple imputation will be used to impute missing data in the ITT analysis. Influx and outflux statistics will be applied to identify factors that will serve as auxiliary variables for the imputation model. Sensitivity analysis will be performed to compare imputed with not imputed data.

The usage behavior data will be analyzed between the intervention and control group and within the intervention group. The analysis between the study groups will be done descriptively. For the analysis within the intervention group, the outlined model will be modified. Therefore, the group variable will be omitted, and a variable that codes usage behavior will replace the group variable in the model on level 2.

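### The hypothesis that more programme use leads to better outcomes is tested on self-chosen use within one arm, with no adjustment of the slope, so the result can support only an association

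*Protocol article*

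**What the plan says.** The Introduction lists three questions. The last concerns programme use, and its hypothesis is that "higher frequency and intensity of program use leads to better primary and secondary outcomes". Section 2.4.3 gives the same purpose for the system data: "To examine the effects of usage behavior on primary and secondary outcomes". The measures are login frequency and duration during the intervention phase, login frequency during follow-up, and, for the intervention arm only, "logged activities (activities/week) (intervention group)".

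Section 4.3 divides the analysis in two. Across arms, "The analysis between the study groups will be done descriptively". Within the intervention arm the mixed model is reused without group: "a variable that codes usage behavior will replace the group variable in the model on level 2". The only inferential test of the third hypothesis is therefore this within-arm model.

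Use is not assigned. Section 2.3.1 describes the programme as offering "interactive, self-directed, and flexible handling", and after completion "the user can repeat the coaching as often as desired until the end of the study period". In the weight module some logged activity is a record of the outcome itself: "Another pre-planned activity is to log body weight and waist circumference every week".

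On confounding, Section 4.3 allows covariates at a level 1 placeholder (X) or a level 2 placeholder (Z), with age and gender as examples.

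**The concern.** In the main analysis the group term is randomised, so its interaction with time has a causal reading. The usage model keeps the same equations but puts a post-randomisation behaviour in that place, and the hypothesis keeps its causal wording. Two other routes lead to the same coefficient:

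- **Confounding.** A motivated participant may log in more and also train or diet more for reasons unrelated to the programme.
- **Reverse causation.** A participant who is already improving sees this on the dashboard and may log more as a result.

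At stake is the conclusion of the third aim. If the plan is followed as written, a significant coefficient would be reported as benefit caused by use, and the model cannot separate use from either route.

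**Working it through.** **1. The plan's own figures.** The article gives no power figure for the usage analysis, so its sample sizes serve only to set the number in the arm. A two-sample t-test with two-sided 0.05 and power 0.80 gives 78.5, hence 79 per arm, at d = 0.45, and 63.8, hence 64, at d = 0.50. Both match Section 2.6. Allowing for 15% dropout, 79/0.85 = 92.9 (stated 93) and 64/0.85 = 75.3 (stated 75). The intervention arm thus has 64–75 in the weight trial and 79–93 in the fitness trial.

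**2. Where covariates enter.** After substitution, the equations in Section 4.3 become:

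- intercept: γ00 + γ01·usage + γ0n·Z + u0
- slope: γ10 + γ11·usage + u1

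The coefficient of interest is γ11. Z stands only in the intercept equation. X is an additive term at level 1, so a fixed characteristic placed there also shifts only the level. Neither placeholder adjusts γ11.

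This was checked by simulating the random-intercept-and-slope model with n = 79, four time points, no true usage effect, and a perfectly measured confounder correlating 0.6 with use and with slope (assumed; 150 runs):

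| Confounder in the model | Mean γ11 | Significant |
|---|---|---|
| absent | 0.352 | 86% |
| at the printed level 2 position | 0.352 | 86% |
| also interacting with time | about 0 | 5% |

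**3. Size of a spurious dose-response from motivation.** Assume motivation correlates r with use and r with change, and use has no effect. The induced correlation between use and change is r × r. With Fisher's z, the chance of significance is about Φ(z − 1.96) + Φ(−z − 1.96), where z = atanh(r²)·√(n − 3).

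- r = 0.3, n = 64: r² = 0.09; z = 0.0902 × √61 = 0.705; chance = 0.109.
- r = 0.6, n = 93: r² = 0.36; z = 0.3769 × √90 = 3.575; chance = 0.947.

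Simulation of the same set-up (20,000 runs per cell) agrees to within about one percentage point:

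| Assumed r | Induced r² | n = 64 | n = 75 | n = 79 | n = 93 |
|---|---|---|---|---|---|
| 0 | 0 | 5% | 5% | 5% | 5% |
| 0.3 | 0.09 | 11% | 12% | 12% | 14% |
| 0.4 | 0.16 | 24% | 28% | 29% | 34% |
| 0.5 | 0.25 | 52% | 58% | 61% | 69% |
| 0.6 | 0.36 | 84% | 89% | 91% | 95% |

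**4. Reverse causation alone.** If progress drives use at an assumed correlation of 0.2, 0.3 or 0.5, significance appears in 36%, 68% or 99% of trials at n = 64, and in 49%, 84% or more than 99% at n = 93.

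Steps 3 and 4 test use against individual change, a simplification of the mixed model.

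**The case against.** Usage is the last aim and is listed under other outcomes. A within-arm usage analysis is a common supplement to a trial, and a condensed article may leave the usage variable and the covariate list to the full plan. Section 4.3 does mention confounders, with age and gender only as examples. All of this is fair, and no finding is made that the list is incomplete. What stands is what the article itself fixes: causal wording, a within-arm test, and a slope equation without covariates.

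Three stronger readings are tempting and are not supported:

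- **That the result would probably be positive whatever the programme does.** This depends wholly on the assumed correlations. At 0.3 the chance is 11–14% and at 0.4 it is 24–34%. The direction is assumed too: participants who reach their goal may stop logging while those who struggle log more.
- **That later use is made to predict earlier outcomes.** Section 2.4.3 records intervention-phase and follow-up use separately. Nothing in the article pools them or relates follow-up use to t1.
- **That weight logging contaminates the outcome.** Body weight is measured on a clinic scale, and the weekly entry is one activity among many, in one trial and in one of the usage measures. It justifies a sensitivity analysis and no more.

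The model also already separates baseline level from change, since t0 is in the outcome vector and usage enters both the intercept and the slope equation. Adjusting for the t0 outcome is therefore not the missing step.

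**Conclusion.** The point holds for the third aim. The planned test cannot support the statement that use leads to better outcomes, and covariates placed as printed would not change that. With no true effect, the false-positive rate would be about 11–14% if motivation correlates 0.3 with both use and change, rising to 84–95% at 0.6, for 64–93 in the arm. It equals the nominal 5% only if neither confounding nor reverse causation operates. The article gives no such correlations, so the range shows sensitivity and is not a forecast. The placement of the covariates follows directly from the printed equations and needs no assumed value. The randomised time-by-group comparison, the primary outcomes and the sample size are untouched.

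**What to change.** 1. State the usage hypothesis, its purpose and its conclusion as an association (Introduction, Sections 2.4.3 and 4.3).
2. In the usage model, add age, gender and baseline physical activity and diet, each with its interaction with time. All are already collected. Do not add the t0 outcome as a covariate while it remains in the outcome vector.
3. Relate intervention-phase use to change after t1 (t1 to t2 and t1 to t3) as the analysis in which exposure precedes outcome, and label the analysis of use against t0–t1 change as concurrent. An early window such as weeks 1–6 would not achieve this ordering, because no outcome is measured between week 0 and week 12.
4. In the weight trial, repeat the logged-activity analysis without weight and waist entries as a sensitivity analysis.

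The cost is some rewording, a slightly longer model and some loss of precision. Change after t1 answers a narrower question, about maintenance after the programme, and the text should say so. Confounding by unmeasured motivation will remain and should be stated as a limitation.

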## 5. Materials and Methods: Monitoring

### 5.1. Data Monitoring

A data monitoring committee (DMC) for the clinical trials (F_clin_, W_clin_) will be established for the recruitment and retention process as the outcomes are associated with low risks. This non-independent DMC will be composed of some of the study staff and the study directors of the involved institutions (SEVERA, DoSS, VHG). However, the trial sponsor (TK) will only be informed about the process and will have no access to any data. There will be no conflicts of interest. As part of the recruitment process, the DoSS will report the current recruitment data of the clinical trials at weekly DMC meetings and will inform the entire project team and the trial sponsor. The report will be done based on the registrations in the back-office system, the telephone screenings, and the medical examinations carried out on-site. If technical or other unforeseen problems arise during the recruitment process, these will be discussed in the DMC and resolved immediately in direct consultation. Based on the report, the entire project team will be able to adjust the recruitment measures and finally decide on recruitment completion. Afterwards, the DoSS will continue reporting at regular DMC meetings and informing the entire project team and the trial sponsor about examined study participants and study dropouts.

### 5.2. Harms

No particular risks are expected in the context of the clinical trials (F_clin_, W_clin_). In rare cases, skin irritation or infection of the puncture site can occur after blood uptake. Furthermore, muscle soreness can occur in the following days after physical fitness assessments or training sessions of the health programs. No other risks are expected.

Apart from that, the study participants will have to agree to the inclusion and exclusion criteria, undergo a detailed screening, and, in case of health problems or diseases, provide a medical certificate attesting their ability to participate in the trial and the health program. Moreover, the potential risks were reviewed by the Ethics Committee of the University of Freiburg and the principal medical investigator of the study.

Adverse and any other events will be documented in a standardized way at the medical examinations. The study participants will be asked to inform the study staff if any event occurs in the interim study phases. Adverse events will be reported to the principal medical investigator of the study and the entire project team. If any event occurs, the study participants will be able to cancel, interrupt, or repeat the medical examinations. They will also have the possibility to cancel, interrupt, or modify the health program. If necessary, immediate care and treatment measures will be initiated by the principal medical investigator. He will also be able to terminate participation prematurely if health problems occur that partially or entirely exclude participating in the trial and the health program. Travel accident insurance, including stays on-site, will be arranged for all study participants.

## 6. Conclusions

This study is part of a nationwide evaluation project. The aim of its two randomized controlled clinical trials (F_clin_, W_clin_) is to investigate short-, medium-, and long-term health effects of a 12-week interactive web-based health program (TK-HC) compared to a 12-week non-interactive web-based health program in physically inactive and overweight or obese adults. An elaborate assessment of objective outcomes will be used to assess health effects. As this study will be conducted during the coronavirus disease 2019 (COVID-19) pandemic, health effects could be affected due to restrictions in daily life. Finally, this study addresses the need for further research on web-based lifestyle interventions.

## Figures and Tables

**Figure 1 ijerph-19-01393-f001:**
[figure not shown]
Dashboard of the “TK-HealthCoach” (TK-HC): (**a**) “TK-FitnessCoaching” (TK-FC); (**b**) “TK-WeightLossCoaching” (TK-WC). Source: Project’s landing page (https://gesundheitsprogramm.tk.de/de/studien/gesundheitsziele (accessed on 21 October 2021)).

**Figure 2 ijerph-19-01393-f002:**
[figure not shown]
Activities of the “TK-HealthCoach” (TK-HC): (**a**) Fitness activities (“TK-FitnessCoaching” (TK-FC)); (**b**) weight loss activities (“TK-WeightLossCoaching” (TK-WC)). Source: Project’s landing page (https://gesundheitsprogramm.tk.de/de/studien/gesundheitsziele (accessed on 21 October 2021)).

**Figure 3 ijerph-19-01393-f003:**
[figure not shown]
Participant timeline of the clinical fitness trial (F_clin_) and the clinical weight loss trial (W_clin_): (**a**) Enrolment process; (**b**) intervention and assessment process.

**Table 1 ijerph-19-01393-t001:** Primary and secondary outcomes of the clinical fitness trial (F_clin_) and the clinical weight loss trial (W_clin_).

Outcome						Measurement Time Point			
						t0 ^1^	t1 ^2^	t2 ^3^	t3 ^4^
primary	health goal achievement	F_clin_	cardiorespiratory fitness		maximum oxygen uptake (VO_2_max) (ml/min/kg)	x	x	x	x
		W_clin_	anthropometry		body weight (kg)	x	x	x	x
secondary	behavioral	F_clin_ W_clin_	physical activity behavior		steps taken (steps/day)	x	x	x	x
					sedentary behavior (minutes/day)				
					physical activity (light, moderate, vigorous intensity) (minutes/week)				
		F_clin_ W_clin_	dietary behavior		energy and nutrient intake (kcal, µg, mg, g, %)	x	x	x	x
					food consumption (HEI-NVS ^5^) (g, ml, score)				
		W_clin_			energy density (kcal/g)				
	physiological	F_clin_	musculoskeletal fitness		maximum isometric strength (N, kg, lbs)	x	x	x	x
		F_clin_	anthropometry		body weight (kg)	x	x	x	x
		F_clin_ W_clin_			body height (cm)				
					body mass index (BMI) (kg/m^2^)				
					fat mass (kg, %)				
					fat-free mass (kg, %)				
					waist circumference (cm)				
secondary	physiological	F_clin_ W_clin_	blood pressure		systolic blood pressure (mmHg)	x	x	x	x
					diastolic blood pressure (mmHg)				
					heart rate (bpm)				
		F_clin_ W_clin_	blood levels	blood lipids	total cholesterol (mg/dL)	x	x	x	x
					LDL ^6^ cholesterol (mg/dL)				
					HDL ^7^ cholesterol (mg/dL)				
					triglycerides (mg/dL)				
				blood glucose	fasting plasma glucose (mg/dL)	x	x	x	x
					HbA1c ^8^ (mol/mol Hb, %)				
		F_clin_ W_clin_	vascular health		endothelial function (FMD) ^9^ (%)	x	x	x	x
					vascular age (days)				

^1^ t0: 0 weeks; ^2^ t1: 12 weeks; ^3^ t2: 6 months after t1; ^4^ t3: 12 months after t1; ^5^ HEI-NVS: Healthy Eating Index of the German National Nutrition Survey; ^6^ LDL: Low-density lipoprotein; ^7^ HDL: High-density lipoprotein; ^8^ HbA1c: Glycosylated hemoglobin; ^9^ FMD: Flow-mediated dilatation.

